### Randomization

The study will use permuted block randomization. A block size of four and an allocation of 1:1 will be adopted. The sequences that have been generated are AABB, ABAB, ABBA, BAAB, BABA, and BBAA, with A as the intervention group and B as the control group. The block sequence will be programmed to ePain and run randomly. The research team cannot modify the sequence and randomization of the sequence in ePain. The team will be blinded to the sequence used to allocate the participants. When the participants register for ePain, they will be assigned at random according to the sequence, and blinded to the sequence.

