### Sample size

The sample size was estimated based on Ruehlman et al. [30], who aimed to examine an Internet-based programme for the self-management of chronic pain in the United States. Their measure of pain intensity was used to calculate the effect size, as their study did not examine self-efficacy. The effect size was calculated to be 0.47. To achieve an effect size of 0.47, a power value of 0.8, and an α value of 5%, 114 participants will be recruited. The drop-out rate has been calculated with reference to Ruehlman et al.’s study examining the efficacy of an online Chronic Pain Management Programme and William et al.’s study evaluating the effects of an Internet-based behavioural self-management programme on fibromyalgia patients [30, 31]. The drop-out rate was 7.5% in Ruehlman et al.’s study and 10% in William et al.’s study [30, 31]. A 30% drop-out rate needs to be considered to obtain an adequate number of participants. Therefore, 148 participants will be recruited, with 74 participants in each group.

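### The 30% drop-out allowance was added as 114 × 1.3 = 148 rather than 114 / 0.7 = 163, so at 30% drop-out the planned recruitment leaves about 104 completers, not 114

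*Protocol article*

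**What the plan says.** The whole calculation stands in one paragraph of the protocol article, under Sample size. The base figure is: "To achieve an effect size of 0.47, a power value of 0.8, and an α value of 5%, 114 participants will be recruited". The effect size comes from pain intensity in an earlier trial of an online programme. The paragraph then gives drop-out rates of 7.5% and 10% from two cited studies, but adopts a larger allowance: "A 30% drop-out rate needs to be considered to obtain an adequate number of participants". It concludes: "Therefore, 148 participants will be recruited, with 74 participants in each group". The inflation formula is not written out, and the paragraph does not say whether the 5% level is one-sided or two-sided. Under Randomization, allocation is 1:1, so 114 means 57 per group.

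**The concern.** The three printed figures, 114, 30% and 148, do not agree if 30% is the proportion of recruits who drop out. That is the ordinary meaning of a drop-out rate, and it is how the same paragraph uses the term for the cited studies. Recruitment of 148 then falls short of the number the paragraph says is needed, at the very rate chosen to protect that number. At stake is whether the stated power of 0.8 for the primary comparison holds under the plan's own assumption, and whether the final report will repeat an allowance that the figures do not support.

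**Working it through.** **Inputs (protocol article, Sample size and Randomization).** Effect size d = 0.47; power 0.80; α = 5%, sidedness not stated; base total 114; drop-out allowance 30%; recruitment 148 (74 per group); 1:1 allocation; cited drop-out 7.5% and 10%.

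**1. Reproducing the base figure of 114.** Normal approximation per group: n = 2(z_α + z_0.80)² / d².
- One-sided 5%: 2(1.645 + 0.842)² / 0.47² ≈ 56 per group. The t-test solution is 56.7, so 57 per group and 114 in total. This matches.
- Two-sided 5%: 2(1.960 + 0.842)² / 0.47² ≈ 71.1, so 72 per group. The t-test solution is 72.04, so 73 per group. The totals of 144 to 146 do not match.

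So 114 is reproduced on a one-sided 5% basis. That is an inference from the numbers; the text does not say it.

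**2. Reproducing 148.** Multiplying by (1 + 0.30):
- 114 × 1.3 = 148.2, and 57 × 1.3 = 74.1 per group. Both match the stated 148 and 74.

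Dividing by (1 − 0.30):
- 114 / 0.7 = 162.9, so 163. Per group, 57 / 0.7 = 81.4, so 82, or 164 in total. Neither matches.

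The allowance was therefore applied by multiplication. The correct figure is 15 to 16 higher than the one stated.

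**3. What 148 delivers.**
- At 30% drop-out: 148 × 0.7 = 103.6, about 104 completers (74 × 0.7 = 51.8 per group). This is about 10 short of 114.
- Highest drop-out that still leaves 114: 1 − 114/148 = 0.230, or 23%.
- At the cited rates: 148 × 0.925 = 136.9 and 148 × 0.90 = 133.2. Both exceed 114.

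**4. Effect on power.** Two-sample t test, single time point, unadjusted, d = 0.47:

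| Basis | 57 per group (114) | 51.8 per group (about 104) | Change |
|---|---|---|---|
| One-sided 5% | 0.802 | 0.768 | −0.034 |
| Two-sided 5% | 0.701 | 0.659 | −0.042 |

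On either basis the drop-out step costs about 3 to 4 percentage points.

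**The case against.** The arithmetic itself is not open to dispute, but its weight is.

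- **The shortfall is conditional.** The only drop-out rates observed in the cited studies are 7.5% and 10%, and 148 covers both with room to spare. The 30% is a margin three times the higher of these. This stands as a limit on severity. It does not reconcile the figures, because the plan chose 30% itself.
- **Drop-outs stay in the analysis.** Under Statistical methods, the analysis is by intention to treat with last observation carried forward, so a reader who infers that the analysed set falls below 114 goes too far. The shortfall is in completers. Carried-forward values do not restore the lost follow-up information, though, and the plan's own inflation step treats drop-out as a loss.
- **The power figures are for a simple t test.** The plan includes t tests at each time point but also generalized estimating equations with a time-averaged comparison, to which these figures do not directly apply. This stands.
- **The Discussion already says the sample size may be too small or too large.** That caveat concerns the effect size borrowed from pain intensity. It does not touch the drop-out step.

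A stronger reading is tempting: that the slip takes power from the stated 0.80 down to 0.66. The figures do not support it. The 0.80 belongs to a one-sided test and the 0.66 to a two-sided one. On a two-sided basis, 114 completers give only 0.70 before any drop-out. The gap between 0.70 and 0.80 comes from the sidedness of the base calculation, which is a separate question.

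**Conclusion.** The point holds. The recruitment figure does not keep 114 completers at the plan's own drop-out rate: 148 leaves about 104, and 163 (164 with equal groups) would have been needed. The loss in power is 0.80 to about 0.77 one-sided, or 0.70 to 0.66 two-sided, and a shortfall below 114 arises only if drop-out exceeds 23%.

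This rests on four assumptions: 114 is accepted as the base; drop-out is a share of those recruited; d = 0.47; and an unadjusted two-group comparison at one time point. It also takes 148 as the number enrolled. The article says that recruitment has ended but gives neither the number reached nor the observed drop-out. So a reader should not infer that the trial actually lost power through this slip. The error is in the stated plan, it is certain, and its numerical effect is modest.

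**What to change.** Under Trial status, recruitment is reported as completed on 1 January 2020, so restate the figure and do not enrol more. Either of two corrections would do:

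1. Say that 148 recruits allow for 23% drop-out while keeping 114 completers, and remove the claim of a 30% allowance.
2. Keep 30%, and state that 148 recruits leave about 104 completers (about 52 per group), with the resulting power.

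In either case, state the sidedness of the 5% level. Under the second option, use the same basis for 114 and 104: 0.80 to 0.77 one-sided, or 0.70 to 0.66 two-sided. Quoting 0.80 for 114 beside 0.66 for 104 would mix the two bases and misattribute the loss. Carry the same wording into the sample size section of the final report.

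The cost is one corrected sentence and a slightly less favourable stated figure. Allocation, outcomes and analysis are unaffected.

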### Data collection methods

As ePain will be an online programme, the data collection procedure will be conducted on the Internet. The participants will use their e-mail addresses to register accounts for individual use. Figure 1 shows the data collection procedure of the study.

**Fig. 1 Fig1:**
[figure not shown]
Data collection procedure for the study. ePain electronic pain management programme

The outcomes will be measured at different time points. All of the outcomes and demographics will be collected at week 1 as the baseline in both groups. At week 3, the process will be evaluated by collecting information about the participants’ pain self-efficacy, pain situation, experience of using ePain, non-pharmacological interventions for pain management, and comments on ePain in the intervention group. At the week 6 post assessment and the week 12 follow-up assessment, both groups will have to finish the same questionnaire as at baseline. Feedback on ePain will be collected at week 6. To minimize the amount of missing data, messages will appear as prompts when the participants submit their questionnaire, reminding them to complete the missed items. The incomplete items will be highlighted in red to invite the participants to complete them. Figure 2 illustrates the schedule of enrolment, interventions, and assessments.

**Fig. 2 Fig2:**
[figure not shown]
Schedule of enrolment, interventions, and assessments

### Data management

The research team will ensure the confidentiality of the data. The questionnaire and ePain will be hosted on Google, and the collected data will be stored on Google Drive. Google provides information security and encryption services [44]. The data will be retrieved from Google Drive and stored on a computer under password protection. The research team will be the only party able to access the Google account and computer. Passwords will be changed on a regular basis. After the study, all of the data on Google Drive will be downloaded and stored in a password-protected computer. The data will then be deleted from Google Drive.

### Statistical methods

The IBM Statistical Package for the Social Sciences (SPSS) for Windows version 25.0 will be used to statistically analyse the quantitative data. Normality checking will be conducted using the Kolmogorov–Smirnov test. For the descriptive data on the demographics and outcome variables, the means, standard deviations, and percentages will be calculated. For continuous variables, the mean and standard deviations will be presented. The median and a centile range will be reported if the continuous variables do not show a symmetrical distribution.

The data will be analysed on an intention-to-treat basis. Generalized estimating equations will be adopted to investigate the time-averaged difference and differences at each follow-up time. An analysis will be conducted of the within-group effect at week 3, week 6, and week 12, and the interaction between the time effect and the group by group effect (group × time) on the outcome variables, including pain self-efficacy, pain situations, negative emotions, and quality of life. An independent-samples *t* test will be conducted for between-group comparisons at week 3, week 6, and week 12. The significance level will be set at 0.05. Missing data will be analysed using Missing Values in SPSS. The last observation carried forward method will be used to replace the missing data [49, 50].

The Consolidated Standards of Reporting Trials (CONSORT) will be adopted to write up the final report.

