### Outcomes

#### Primary outcome

The primary outcome is pain self-efficacy, which will be measured using the Pain Self-Efficacy Questionnaire at weeks 1, 3, 6, and 12. The questionnaire will contain 10 items. A 7-point scale will be used for measurement, ranging from 0 (not at all confident) to 6 (completely confident), with higher marks representing stronger self-efficacy beliefs. The Cronbach’s α coefficient of the measure of the internal consistency of the items is 0.92 [40]. The Chinese version of the Pain Self-Efficacy Questionnaire (PSEQ-HK) has a Cronbach’s α coefficient of 0.93. Its test–retest reliability coefficient is 0.75, and the SF-36BP and the PSEQ-HK are significantly correlated, with *r* = 0.402 [41].

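### Baseline scores are collected from everyone, but the planned t tests ignore them and the GEE names no baseline covariate; adding one is an almost free gain in precision

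*Protocol article*

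**What the plan says.** All quotations are from the protocol article.

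- **Statistical methods, GEE.** "Generalized estimating equations will be adopted to investigate the time-averaged difference and differences at each follow-up time". The section then lists within-group effects at weeks 3, 6 and 12 and a group × time interaction. It names no baseline covariate and does not say whether week 1 is a level of time.
- **Statistical methods, t tests.** An independent-samples t test "will be conducted for between-group comparisons at week 3, week 6, and week 12". The section does not say whether the t tests or the GEE give the governing between-group result.
- **Data collection methods (text under Fig. 1).** All outcomes are collected at week 1 in both arms. The week 3 assessment is described for the intervention arm only, and the Control group section lists only weeks 6 and 12 after baseline.
- **Primary outcome.** For the PSEQ-HK: "Its test–retest reliability coefficient is 0.75". No correlation between baseline and week 6 or week 12 is given.
- **Sample size.** "To achieve an effect size of 0.47, a power value of 0.8, and an α value of 5%, 114 participants will be recruited". The target is then raised to 148 (74 per arm) for 30% drop-out. On the source of the effect size: "Their measure of pain intensity was used to calculate the effect size, as their study did not examine self-efficacy".

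**The concern.** A participant's own baseline score usually predicts the follow-up score on the same scale. A t test on follow-up scores leaves that explained variation in the error term, and any chance baseline difference between arms stays in the estimate. The GEE might use baseline through a week 1 level of time, or might not use it at all; the text does not settle which. In neither case is it the most precise use of data already in hand.

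At stake is power for the primary comparison. There is also a choice of estimate: raw, change and adjusted analyses can give different answers, and the plan does not say which one counts.

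**Working it through.** **Inputs.** d = 0.47 and 5% significance (Sample size; "The significance level will be set at 0.05" in Statistical methods). 1:1 allocation. 74 per arm recruited. With the planned 30% loss, 148 × 0.70 = 103.6, taken as 52 per arm. Assumptions: two-sided testing (sidedness is not stated), equal SD at baseline and follow-up, and a baseline to follow-up correlation r between 0.3 and 0.75. The upper end borrows the test-retest coefficient as an optimistic value.

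**Step 1: the plan's own figure.** For d = 0.47 and 80% power, the t-test calculation gives 56.7, so 57 per arm (114 in total), one-sided. Two-sided it gives 72.04, so 73 per arm (146). The stated 114 therefore reproduces only one-sided. The 148 is 114 × 1.3 = 148.2.

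**Step 2: variance of the group contrast, relative to the raw follow-up comparison.**

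- Raw t test: 1.
- Change from baseline, which is what group × time estimates if week 1 is a level of time: 2(1 − r).
- Baseline as a covariate: 1 − r² = (1 − r)(1 + r).

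Covariate adjustment relative to change is (1 − r²)/[2(1 − r)] = (1 + r)/2, which is below 1 for every r below 1. Relative to the raw comparison it is 1 − r², which is below 1 for every nonzero r. The change contrast equals the raw comparison at r = 0.5 and is worse below that.

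| r | Change, 2(1 − r) | Adjusted, 1 − r² | Adjusted ÷ change |
|---|---|---|---|
| 0.3 | 1.40 | 0.91 | 0.65 |
| 0.5 | 1.00 | 0.75 | 0.75 |
| 0.6 | 0.80 | 0.64 | 0.80 |
| 0.75 | 0.50 | 0.44 | 0.875 |

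**Step 3: power.** The effective effect size is 0.47 divided by the square root of the variance factor. At r = 0.6, for example, the adjusted value is 0.47/√0.64 = 0.5875. Noncentral t, two-sided 5%:

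| Per arm | Analysis | r = 0.3 | r = 0.5 | r = 0.6 | r = 0.75 |
|---|---|---|---|---|---|
| 52 | Raw t test | 0.66 | 0.66 | 0.66 | 0.66 |
| 52 | Change contrast | 0.52 | 0.66 | 0.76 | 0.92 |
| 52 | Baseline-adjusted | 0.70 | 0.78 | 0.84 | 0.95 |
| 74 | Raw t test | 0.81 | 0.81 | 0.81 | 0.81 |
| 74 | Change contrast | 0.67 | 0.81 | 0.89 | 0.98 |
| 74 | Baseline-adjusted | 0.85 | 0.91 | 0.94 | 0.99 |

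**Step 4: the two readings of the GEE.** If week 1 is a level of time, the interaction is the change contrast above, and a time-averaged difference that included week 1 would mix a pre-treatment comparison into the effect. If week 1 is not a level of time, baseline is unused and the raw rows apply to each single follow-up. Adjustment is more precise on both readings.

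**The case against.** **The GEE may already use baseline.** Within-group effects at weeks 3, 6 and 12 need a reference, and week 1 is the natural one, so week 1 probably enters as a repeated outcome. The interaction would then remove chance baseline imbalance. This stands: a reader might infer that the GEE ignores baseline, but the text does not show that. The imbalance complaint is secure only for the t tests. The point survives because a change contrast is still less precise than adjustment. At r = 0.75, however, the gain over it is only 0.92 to 0.95 at 52 per arm, far less than the 0.66 to 0.95 against the raw t test.

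**The trial is not shown to be underpowered.** That label is tempting but conditional. It needs a two-sided test and real loss to follow-up. Power is about 0.81 if all 148 are analysed, which last observation carried forward nominally allows, and 0.77 to 0.78 at the cited drop-out of 10% to 7.5%. Carrying values forward keeps the rows but does not supply the missing observations, so 0.81 is a nominal figure. The effect size comes from pain intensity, and the Discussion concedes that the sample size may be an underestimate or an overestimate. The case for adjustment does not depend on a shortfall.

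**The gain rests on an assumed correlation.** This stands. Test-retest reliability is not a correlation over 6 to 12 weeks under intervention, and it does not establish that baseline is strongly predictive here. At r = 0.3 the gain over the t test at 52 per arm is only 0.66 to 0.70.

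**The planned tests are valid.** This stands too. Under randomisation the unadjusted comparison is unbiased and its standard error already allows for chance imbalance.

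**Covariate lists belong in an analysis plan.** This is partly right for the GEE. The t tests, however, are a stated choice that excludes baseline.

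**Conclusion.** The point holds as an efficiency improvement, not as an error that invalidates the analysis. The t tests ignore a baseline that is collected from everyone, and the GEE text does not say how baseline enters. Baseline adjustment is more precise than the raw comparison for every nonzero r and than a change contrast for every r below 1.

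Over the assumed range r = 0.3 to 0.75 it cuts variance by 9% to 56% against the t test (1 − 0.91 and 1 − 0.4375) and by 35% to 12.5% against a change contrast (1 − 0.65 and 1 − 0.875). The power gain over the t test is 0.04 to 0.29 at 52 per arm and 0.04 to 0.18 at 74 per arm. These sizes depend on d = 0.47, two-sided testing, equal SDs and the assumed r, so the documents support the direction of the gain but not one figure for it.

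**What to change.** Record by dated amendment, before any comparative result is seen:

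1. The primary model is a GEE (or mixed model) with PSEQ-HK at weeks 6 and 12 as responses, and group, time, group × time and baseline PSEQ-HK as covariates. It supplies both the time-averaged difference and the difference at each of the two visits.
2. Each secondary scale is analysed in the same way with its own baseline.
3. The independent-samples t tests are dropped or labelled descriptive, so that one estimate governs.
4. Week 3 is left out of the between-group model, because the Control group and Data collection sections describe no week 3 assessment in the control arm. Week 3 data can be reported within the intervention arm.

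The change needs no further participants or data, and SPSS fits the model directly. The cost is the amendment itself. Recruitment closed on 1 January 2020 according to Trial status, so the amendment should give its date, its reason and confirmation that no comparative results had been examined. If they had been, the adjusted model should be reported as a sensitivity analysis.

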### Control group

The control group participants will be able to download a pain education pamphlet after completing the baseline assessment. The pain pamphlet will contain information from the session ‘Introduction to pain’, which will discuss the definition of pain, pain theories, and factors contributing to pain. They will also need to complete the post assessment at week 6 and the follow-up assessment at week 12. ePain will be open to the participants after they complete the follow-up assessment.

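### Pain self-efficacy is tested by overlapping between-group analyses, each at 0.05, and none is named as deciding; if any one may carry the claim, the false-positive chance is roughly 1.4 to 3.4 times 0.05

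*Protocol article*

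**What the plan says.** *Primary outcome* defines the endpoint by instrument and visits: "The primary outcome is pain self-efficacy, which will be measured using the Pain Self-Efficacy Questionnaire at weeks 1, 3, 6, and 12". No visit is singled out.

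*Statistical methods* then lists, for this outcome and the others:

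- a GEE analysis: "Generalized estimating equations will be adopted to investigate the time-averaged difference and differences at each follow-up time";
- within-group effects: "An analysis will be conducted of the within-group effect at week 3, week 6, and week 12";
- a group × time interaction "on the outcome variables, including pain self-efficacy, pain situations, negative emotions, and quality of life";
- parallel two-sample comparisons: an independent-samples t "test will be conducted for between-group comparisons at week 3, week 6, and week 12".

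A single sentence sets the error level: "The significance level will be set at 0.05". No order, hierarchy or adjustment is stated.

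The week-3 comparison has a further difficulty. *Control group* gives the controls two assessments after baseline: "They will also need to complete the post assessment at week 6 and the follow-up assessment at week 12". *Data collection methods* lists the week-3 items, ending with "non-pharmacological interventions for pain management, and comments on ePain in the intervention group".

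**The concern.** The between-group question on PSEQ is put in up to four ways: the time-averaged difference, the difference at each visit, the interaction, and the t test at each visit. Each carries the full 0.05. The methods need not agree. A t test compares raw scores at a visit, whereas a GEE visit difference read through group × time compares changes from baseline. A report could therefore hold one significant and one non-significant result for the same visit, with nothing in the plan to say which one answers the question.

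What is at stake is the meaning of the primary result. If the authors may point to whichever visit or model reaches 0.05, then 0.05 is not the error rate of the primary claim. This is more than missing detail, because the article prescribes competing analyses. A later document that named one deciding test would have to demote the rest of this list.

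**Working it through.** **The plan's own figure.** The article states no overall error rate. The nearest figure is the sample size of 114 (effect size 0.47, power 0.8, α 5%). A two-sample t test needs 56.7, so 57 per arm, at one-sided 5%: 2 × 57 = 114, which matches. At two-sided 5% it needs 72.04, so 73 per arm: 2 × 73 = 146. The 148 follows from 114 × 1.3 = 148.2. The sidedness is a separate matter. What counts here is that the calculation supports one two-group comparison and does not say which one.

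**Inputs for the error rate.**

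- Level 0.05 per test (*Statistical methods*), taken as two-sided, critical value 1.96. The article does not state the sidedness.
- Visits: baseline and weeks 6 and 12, the occasions at which both groups are described as assessed.
- Between-visit correlation ρ: not given. The only related figure is a test–retest reliability of 0.75 (*Primary outcome*). Assumed range 0.3 to 0.9, equal between all visits.

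**Statistics.** Let Z0, Z6 and Z12 be the standardised between-group differences under no effect, each with variance 1 and pairwise correlation ρ.

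- t test at visit k: |Zk| > 1.96.
- Time average: |Z6 + Z12| / √(2(1 + ρ)) > 1.96.
- Change from baseline at visit k: |Zk − Z0| / √(2(1 − ρ)) > 1.96.
- Omnibus group × time: Wald statistic on (Z6 − Z0, Z12 − Z0), 2 degrees of freedom, > 5.99.

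If the GEE visit differences are read as raw differences instead, they repeat the t tests and add almost nothing.

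**Results.** Chance of at least one significant result under no effect (2,000,000 draws per row):

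| ρ | Two t tests | + time average | + time average + omnibus | + time average + both change contrasts | All of these |
|---|---|---|---|---|---|
| 0.3 | 9.5% | 10.5% | 13.3% | 16.9% | 17.2% |
| 0.5 | 9.1% | 9.7% | 13.0% | 16.7% | 17.1% |
| 0.75 | 8.1% | 8.3% | 12.3% | 16.0% | 16.6% |
| 0.9 | 7.1% | 7.1% | 11.5% | 15.3% | 16.0% |

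As a check, two independent tests would give 1 − 0.95² = 9.75%, and the two-t-test column lies below that bound.

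As multiples of 0.05, the smallest value is 7.1 / 5 = 1.4 and the largest 17.2 / 5 = 3.4.

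**One visit only.** At week 6 with ρ of 0.5 to 0.75, the raw t test and the change contrast reach different verdicts in about 8% to 9% of null trials, and at least one is significant in about 9%. Naming a visit without naming a method therefore does not restore 0.05.

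**The case against.** The strongest reply is that nothing in the article says success means any one significant test. That is correct. The percentages describe what the stated plan permits, not what it prescribes, and the multiple depends on which tests are allowed to count. With the t tests and the time average alone it is 1.4 to 2.1 times (7.1 / 5 to 10.5 / 5). The interaction can fairly be read as one test, which gives 2.3 to 2.7 times (11.5 / 5 to 13.3 / 5). Only separate change contrasts take it to 3 or above.

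A second reply is that the abstract names only GEE, so the t tests may be supplementary, and that an analysis plan not shown may name the deciding contrast. This stands in part. GEE can reasonably be read as the main method. Which GEE contrast decides is still open, however, and the article itself sets the t tests beside it at the same level.

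Three stronger readings are tempting and are not supported:

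- A reader might count three between-group visits and infer a higher rate. The article describes week-3 data for the intervention group only, so a week-3 comparison has no described control data and is left out of the figures.
- A reader might infer that within-group improvement will be offered as proof that ePain works. The article lists those tests but never calls them evidence of effect.
- A reader might add the pain, mood and quality-of-life scales to the count. They are already labelled secondary under *Secondary outcomes*.

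**Conclusion.** The point holds in this form: overlapping between-group tests of the primary outcome share one 0.05 level, with no primary time point, deciding contrast or order. If any of them may support the primary claim, the false-positive chance from weeks 6 and 12 alone is about 7% to 17%, or 1.4 to 3.4 times 0.05. The range reflects the choice of tests more than the correlation. It rests on two-sided tests, equal correlation of 0.3 to 0.9 between visits, and an any-test success rule that the article neither states nor excludes. It would be too strong to say that the trial's error rate is two to three times nominal, because no decision rule is written down. The structural fault is certain; its size is conditional. The week-3 between-group test is a separate internal conflict that needs reconciling.

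**What to change.** Before analysis:

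1. Name one deciding between-group PSEQ contrast from a baseline-adjusted GEE, tested at 0.05 with the sidedness stated. Week 6, the end of the 6-week programme, is one natural choice. The time-averaged difference is equally acceptable if fixed in advance.
2. Make the remaining time points and the interaction secondary, tested in a stated fixed order.
3. Drop the parallel t tests.
4. Report within-group changes descriptively, with confidence intervals.
5. Remove the week-3 between-group test, or reconcile it with *Control group* and *Data collection methods*.

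This changes wording only and needs no new data or participants. The cost is that a result significant only on a non-deciding contrast could not be called the primary success.

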### Intervention group

The participants in the intervention group will enter ePain after completing the baseline assessment and randomization at week 1. They will be able to access all of the contents of ePain throughout the study period. They will complete the process evaluation at week 3, the post assessment at week 6, and the follow-up assessment at week 12.

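### A between-group test is planned at week 3, but the arm-specific schedule has only the intervention group assessed then, so the contrast has no scheduled control data

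*Protocol article*

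**What the plan says.** **Analysis.** The Statistical methods section plans an independent-samples t test that "will be conducted for between-group comparisons at week 3, week 6, and week 12". It also states: "Generalized estimating equations will be adopted to investigate the time-averaged difference and differences at each follow-up time". A within-group effect is planned at weeks 3, 6 and 12, together with a group × time interaction, "on the outcome variables, including pain self-efficacy, pain situations, negative emotions, and quality of life". Missing data are to be replaced by last observation carried forward (LOCF).

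**Schedule by arm.** For the intervention group: "They will complete the process evaluation at week 3, the post assessment at week 6, and the follow-up assessment at week 12". For the control group, after the baseline assessment: "They will also need to complete the post assessment at week 6 and the follow-up assessment at week 12". The text under Fig. 1 in Data collection methods describes week 3 as a process evaluation: "At week 3, the process will be evaluated by collecting information about the participants’ pain self-efficacy, pain situation, experience of using ePain", then "non-pharmacological interventions for pain management, and comments on ePain in the intervention group". It names both groups only for weeks 6 and 12.

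**Schedule without an arm.** The Primary outcome section gives pain self-efficacy, "which will be measured using the Pain Self-Efficacy Questionnaire at weeks 1, 3, 6, and 12". The Abstract and the e-mail prompts described under Contents of ePain also mention week 3 for participants in general.

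**The concern.** The analysis asks for a comparison that the visit schedule does not supply. An analyst who follows the protocol has two options at week 3. One is to find that the control arm has no values and drop the test. The other is to treat the empty control cells as missing data and fill them with baseline scores under the LOCF rule.

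The second option would compare real week 3 scores with scores frozen at baseline. Natural course, regression to the mean and repeat testing affect both groups, yet would be credited to ePain. This would touch the primary outcome at week 3 and, through it, the time-averaged difference.

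**Working it through.** **1. Tally of scheduled assessments** (Intervention group, Control group and Data collection methods sections; 74 per group from Sample size)

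| Time | Intervention | Control | Measures listed |
|---|---|---|---|
| Baseline | yes | yes | all outcomes |
| Week 3 | yes | none stated | self-efficacy, pain situation, process items |
| Week 6 | yes | yes | same questionnaire as at baseline |
| Week 12 | yes | yes | same questionnaire as at baseline |

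The week 3 contrast has up to 74 intervention observations and 0 of 74 scheduled control observations. DASS-21 and WHOQOL-BREF (HK) are absent at week 3 in both columns, so the planned within-group week 3 effect on negative emotions and quality of life has no data in either arm.

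**2. No imputation.** The t test cannot be run and the week 3 group × time term is not estimable. Group differences at weeks 6 and 12 can still be estimated.

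**3. LOCF applied to the unscheduled control visits.** The protocol gives no figure for this contrast, so there is none to reproduce. Assumptions: SD 1, no treatment effect, a shift of *d* SD from baseline to week 3 common to both arms, no drop-out, two-sided 5% test (the protocol gives 0.05 without sidedness).

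- Expected difference = (baseline mean + *d*) − baseline mean = *d*, all of it bias.
- Noncentrality = *d* × √(74/2) = 6.083 *d*.

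| Assumed *d* (SD) | Noncentrality | False-positive rate, week 3 t test | Bias in an equally weighted three-visit average, *d*/3 |
|---|---|---|---|
| 0 | 0 | 5% | 0 |
| 0.1 | 0.61 | 9% | 0.03 |
| 0.2 | 1.22 | 23% | 0.07 |
| 0.3 | 1.82 | 44% | 0.10 |

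Simulation (20,000 runs per setting, baseline-to-week-3 correlation 0.5 and 0.75) agrees with the analytic t-test values to within half a percentage point.

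**4. With drop-out, and the carry-over into weeks 6 and 12.** Assume cumulative drop-out of 10%, 20% and 30% at weeks 3, 6 and 12, with *d* = 0.2 by week 3 and 0.3 by weeks 6 and 12.

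- Week 3 bias: 0.9 × 0.2 = 0.18 SD.
- The 10% who leave between weeks 3 and 6 carry a week 3 score in the intervention arm but a baseline score in the control arm. This adds 0.1 × 0.2 = 0.02 SD at week 6 and again at week 12.
- Those who leave between weeks 6 and 12 carry week 6 in both arms and add nothing.
- Time average: (0.18 + 0.02 + 0.02)/3 = 0.073 SD. A simulation of 6,000 null trials at correlation 0.6 gives the same 0.073, with about 20% false positives for the week 3 t test and about 8% for the time average.

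Of the 0.073 SD, 0.18/3 = 0.060 comes from week 3 itself and 0.013 from the unequal carry-forward at the later visits. The second part would remain if only the week 3 test were deleted.

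**The case against.** **Controls may have been assessed at week 3.** No sentence says controls are assessed only at weeks 6 and 12. The closing words of the week 3 sentence could be read as limiting only the ePain-specific items. Three places mention week 3 without naming an arm, and the figures for the data collection procedure and assessment schedule are not visible here. This stands as a reason to check before deleting anything. It does not remove the conflict: none of these places states a control assessment at week 3, the arm-specific sections agree with one another, and if control data were collected, those sections are what need correcting.

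**Week 3 is not attached to every analysis.** The protocol ties week 3 expressly to the t test and the within-group effect. The group × time clause names no weeks, and a week 3 GEE difference is implied only by the reference to each follow-up time. This stands; the express contradiction is the t test.

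**The inflated error rates need a step the protocol does not take.** A reader might infer that the plan will produce false-positive rates of 20% to 44% at week 3. The documents do not support that. LOCF is prescribed for missing data, and nothing says that a visit never scheduled counts as missing. Without that step the result is a test that cannot be run. The shared shift is also an assumption; at zero shift the rate is the nominal 5%. Rates for a change-from-baseline contrast would be higher, but the protocol names no such contrast, so they are not relied on.

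**Weeks 6 and 12 have data in both arms,** and week 3 is not named as the primary time point. This stands and limits the consequence.

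**Conclusion.** The contradiction holds: the protocol plans a between-group t test at week 3, and its arm-specific sections schedule no control assessment then. As written, that contrast has no scheduled control data and cannot be estimated. The planned week 3 within-group effect on negative emotions and quality of life has no data in either arm.

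The size of any bias is conditional. Only if LOCF is applied to the unscheduled control visits, and only if scores shift in both arms, does the week 3 test mislead: about 9%, 23% and 44% false positives at shared shifts of 0.1, 0.2 and 0.3 SD with 74 per group and no drop-out, and one third of the shift in an equally weighted time average. The documents supply neither the shift nor the correlation between visits.

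It would go too far to conclude that the week 6 and week 12 comparisons are invalid. Both arms are assessed at those visits; the only route by which this point reaches them is a week 3 score carried forward in one arm alone.

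**What to change.** 1. Establish whether control participants completed any week 3 assessment. If they did, correct the Control group and Data collection methods sections and keep the week 3 comparison for self-efficacy and pain.
2. If they did not, limit the between-group t tests, the group × time effect and the time-averaged difference to weeks 6 and 12 (with baseline), and amend the Primary outcome section to say that week 3 is measured in the intervention group only.
3. Report week 3 self-efficacy and pain as process data within the intervention group. Drop the week 3 effect for negative emotions and quality of life, which are not listed at that visit.
4. State that control week 3 values are not imputed, and that intervention week 3 values are not carried forward to weeks 6 or 12, so that missing data are handled alike in both arms.

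The cost is wording in the Primary outcome and Statistical methods sections, plus the loss of a week 3 comparison that could not validly be made. Adding a control questionnaire at week 3 is not a practical alternative, since Trial status reports that recruitment was completed on 1 January 2020.
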